### Blinding

Considering that most participants may have learned before the clinical trial that quadriceps strengthening exercise is a treatment for knee OA and that the group allocation can be revealed based on the interventional exercises, the participants will not be blinded to the treatment [16]. However, they will be blinded to the study hypotheses. As questionnaire-based outcomes are self-reported and participants are not blinded to treatments, the assessors of questionnaires will not be blinded. Since the physical performance tests are held in other enclosed rooms, assessors who collect physical function outcomes will be blinded. Statisticians who perform statistical analyses will be blinded. If there will be any unexpected adverse event caused by the exercise program, randomization allocation can be immediately unblinded by the study oversight committee.

### Interventions

Both the leg swing exercise and quadriceps strengthening exercise groups will receive group-based exercise training in the orthopedic outpatient department. The physiotherapist will assess the range of motion and the consistency of movement during follow-up visits. Then the intensity of the exercise program will be adjusted according to each participant’s physical condition. Participants will be required to perform exercise at home every day for 12 weeks. All participants are not allowed to perform any additional exercise program for the treatment of knee OA during the clinical trial.

#### Experimental group

The experimental group will receive leg swing exercise training. That is, participants will be instructed to swing the affected leg. To begin the exercise, participants should stand on a platform approximately 10 cm above the ground (Fig. 2). With the unaffected leg standing on the edge of the platform, the affected side of the lower limb will be free in the air. Then the physiotherapist will instruct participants to raise the affected leg to about 45° from the vertical line and to swing the leg to the back of the participants. During exercise, participants should fully relax, thereby adjusting their breathing rhythm, raising the tongue against the palate, and closing their mouth based on the Chinese traditional medicine theory. Once participants are familiar with the whole exercise, the physiotherapist will encourage them to swing the leg to about 60° from the vertical line. Simultaneously, participants must use one or two sides of the handrails to maintain balance. Then they will be required to swing their leg approximately 1000 times (back and forth = one time) per day [11]. The adjustment of training intensity will be based on the physiotherapist’s discretion during follow-up visits to fit each individual. If participants find it difficult to stand on one leg for quite some time, they are encouraged to train the alternative leg and take interval breaks during the whole exercise program. Thus, training time can be extended appropriately.

**Fig. 2 Fig2:**
[figure not shown]
Diagram of the leg swing exercise

#### Control group

Participants in the control group will receive quadriceps strengthening exercise training. The specific type of exercise program is straight leg raise. To begin the exercise, participants must lie in supine position and keep their legs straight with a weight attached around the ankle of the affected limb. Meanwhile, they should bend the good limb and make sure both the kneecap and toes of the affected limb are pointing toward the ceiling. Afterwards, participants will be required to slowly raise the affected limb straight up until it gets to about 25–30 cm away from the bed. They should stay in this position for 10 s and then slowly lay down over about 3 s [23, 24]. The participants will be required to perform the exercise as a set of 10 repetitions, for 10 sets each time twice a day [24, 25]. The attached weight for the quadriceps strengthening exercise will be determined by asking participants their level of effort, which should be 5–8 out of 10 (hard to very hard) on the modified Borg RPE CR-10 scale [20, 21].

Participants in both groups will have to visit the physiotherapist at the orthopedic outpatient department of Shanghai Jiao Tong University Affiliated Sixth People’s Hospital for an individual session six times within the next 24 weeks.

### Patient and public involvement

Patients are not involved in recruitment. Moreover, the authors developed the research questions and designed the outcome measures without the help of patients and the public. We asked eight patients with knee OA to perform leg swing and straight leg raise exercises to test the safety of the interventions and the feasibility of the study design. The intensity of interventions was modified according to physical performance and feedback provided by the patients. We adjusted the week 1 plan of the 12-week exercise program to help participants adapt to the intensity of the training as quickly as possible. The physiotherapist will keep in contact with the patients through WeChat and instruct them to gradually increase the amount of exercise performed every day. On the basis of the originally planned outpatient follow-up during study weeks 3, 6, and 9, the week of outpatient follow-up will be added. This will be performed not only to urge patients to do the exercise and improve adherence but also to allow the physiotherapist to confirm that the patients can achieve the required amount of training. The findings of the study will be disseminated to the participants and the public.

### Outcome measures

Table 1 shows the outcomes and the time points for assessment. The primary outcomes are person-centered, reliable, and valid measures recommended for knee OA trials [16, 26].

**Table 1 Tab1:** Schedule for data collection

Assessments	Baseline	Home exercise program	Follow-up	
		Weeks 1, 3, 6, 9	Week 12	Week 24
Descriptive data	√			
Imaging (K-L grade, HKA angle, JLCA)	√			√
**Adherence**				
Adherence (11-point NRS)		√	√	
Adherence (EARS)		√	√	
Physiotherapy sessions attended (outpatient records)		√	√	
Adherence (WeChat app records)		√	√	
**Primary outcomes**				
Average knee pain in the past week (VAS)	√		√	√
Physical function in the past week (WOMAC)	√		√	√
**Secondary outcomes**				
Average knee pain upon walking in the past week (VAS)	√		√	√
Pain (KOOS)	√		√	√
Other symptoms (KOOS)	√		√	√
Sport and recreational activities (KOOS)	√		√	√
Knee-related quality of life (KOOS)	√		√	√
Improvement in pain (PPSI)			√	√
Improvement in physical function (PPSI)			√	√
Improvement in general (PPSI)			√	√
Health-related quality of life (AQoL 6D)	√		√	√
Physical activity (PASE)	√		√	√
Physical performance (6-step Stair-Climb and Descent Test)	√		√	√
Physical performance (five times sit to stand test)	√		√	√
Physical performance (Stand on one leg test)	√		√	√
Physical performance (40-m fast-paced walk test)	√		√	√
Physical performance (four square step test)	√		√	√
Muscle strength (knee extensors)	√		√	√
Muscle strength (knee flexors)	√		√	√
Muscle strength (hip abductors)	√		√	√
**Additional measures**				
Use of medication	√	√	√	√
Adverse events		√	√	√

#### Descriptive data

Descriptive data include age, sex, duration of knee OA symptoms, affected side of knee OA, previous treatments for knee and other joints, history of other chronic diseases, current use of medication, history of diseases in other joints, current employment status, and expectation of treatment outcome. Information will be collected at baseline in the orthopedic outpatient department. Height and body mass will be evaluated in the outpatient department and body mass index will then be calculated.

#### Imaging outcomes

Kellgren-Lawrence grade (K-L grade) [27], hip-knee-ankle (HKA) angle, and joint line convergence angle (JLCA) will be assessed via standing full-length radiography conducted by the orthopedic doctor. Radiography will be performed again during follow-up visits 24 weeks after starting the intervention.

#### Primary outcomes

The primary outcomes are average overall knee pain assessed using the visual analog score (VAS) and physical function in daily life assessed using the Western Ontario and McMaster Universities (WOMAC) Osteoarthritis Index (Likert version 3.1).

##### Overall knee pain

The average overall knee pain intensity in the last week will be self-reported by participants using the 100-mm VAS, with terminal descriptors of “no pain” (score 0) and “worst pain imaginable” (score 10) [19].

##### Physical function

The WOMAC Osteoarthritis Index (Likert version 3.1) [28] will be used to assess the physical function of participants in daily life within the last week. This index is a self-reported, disease-specific instrument with high reliability, validity, and responsiveness [29]. The daily physical function subscale contains 17 questions, which include most physical activities in social life. These questions are with Likert response options ranging from “no problems” (score 0) to “extreme problems” (score 4), and the total score ranges from 0 to 68, with higher scores indicating worse physical function. The WOMAC physical function subscale has been included in the Knee injury and Osteoarthritis Outcome Score (KOOS) [30, 31] questionnaire.

#### Secondary outcomes

The secondary outcomes include average knee pain upon walking; KOOS; Patient-Perceived Satisfactory Improvement (PPSI); Assessment of Quality of Life 6-Dimension (AQoL-6D) and Physical Activity Scale for the Elderly scores (PASE); 6-Step Stair-Climb and Descent Test, Five Times Sit To Stand Test (FTSST), Stand on One Leg Test, 40-m Fast-Paced Walk Test, and Four Square Step Test results; muscle strength of lower limb; and adherence.

##### Walking pain

The average knee pain intensity upon walking within the last week will be self-reported by participants using the 100-mm VAS with terminal descriptors of “no pain” (score 0) and “worst pain imaginable” (score 10) [19].

##### Knee injury and osteoarthritis outcome score

Other than the assessment of physical function in daily life (WOMAC), the KOOS questionnaire includes other four subscales: pain (nine questions), other symptoms (seven questions), function in sport and recreation (five questions), and knee-related quality of life (four questions) [30, 31]. Every subscale is scored separately with Likert response options from “no problems” (score 0) to “extreme problems” (score 4). The sum of the questions will be calculated. Then the scores of each part will be transformed to a 0–100 scale, with 0 indicating extreme knee problems and 100 indicating no knee problems.

##### Patient-perceived satisfactory improvement

PPSI is a clinically relevant and stable concept for assessing truly meaningful improvements among patients with knee OA. In this study, changes in knee pain, physical function, and overall condition since the start of the intervention will be self-reported by participants using 7-point Likert scales. The terminal descriptors range from “very much worse” to “very much improved” [32]. Participants reporting that they are “much improved” or “very much improved” will be classified as clinically improved.

##### Health-related quality of life

The AQoL-6D contains 20 items that cover six domains including independent living, mental health, relationships, coping, pain and senses [33, 34]. The AQoL utility score ranges from -0.04 (health state worse than death) to 0.00 (death) and 1.00 (completely healthy) with higher scores indicating a better quality of life. AQoL-6D has been previously used in evaluating the impact of an exercise-based intervention on quality of life among patients with OA [24, 35]. This questionnaire is with low respondent burden, low administrator burden, high psychometric properties, and high responsive level [34].

##### Physical activity

Physical activity assessment will be performed using the PASE [36]. This questionnaire assesses both the level and type of recreational and occupational physical activity undertaken by participants within the last week.

##### Physical performance

Six-step Stair-Climb and Descent Test

Participants will be required to ascend and descend six stairs as fast as possible. The use of one handrail is permitted if required [37]. The time taken to finish the test will be recorded. A shorter time to complete the test indicates a greater physical function.

Five Times Sit to Stand Test

In this test, participants sit on an armless chair with their backs resting against it. Then, they are instructed to stand up and sit down without touching the chair’s arms and back. The time taken to complete five repetitions (up and down = one repetition) will be recorded [37, 38]. A shorter time to complete the test indicates a greater physical function.

Stand on One Leg Test

Participants try to stand on one leg while looking straight ahead. They will be instructed to keep hands on their hips. The number of seconds they can hold the posture up to a maximum of 30 s will be recorded. Timing is stopped when participants move their hands off the hips or put a foot down [39]. Two attempts will be allowed with the best time taken as the score. A longer time indicates a greater ability to maintain balance.

Forty-meter Fast-paced Walk Test:

Participants will be instructed to walk 4 × 10 m (excluding turns) quickly but safely. Walking aids can be used and the results will be recorded. The total time taken to complete the task will be recorded. Then the walking speed will be calculated in meters per second (m/s) [40]. A higher walking speed indicates a greater ability of walking short distances and controlling balance.

Four Square Step Test

Four squares are created on the ground using four walking sticks. Participants will be instructed to step into each square as fast as possible while facing forward. The time taken to complete a full sequence will be recorded [41]. Two attempts will be allowed with the best time taken as the score. If participants lose balance or contact a stick, they can have one more attempt. A higher score indicates a greater physical function.

##### Muscle strength

The maximum voluntary isometric strength of the knee extensors, knee flexors, and hip abductors will be measured using the Baseline 250-lb 12-0399 Push-Pull Dynamometer (Fabrication Enterprises Inc., USA). Assessors will show participants the movement that should be tested first. Then the participants will be instructed to confirm the movement. For each muscle strength test, after a warm-up comprising one submaximal and one maximal contractions, participants must perform three consecutive maximal muscle contractions. Each contraction should be performed within 3–5 s. Between each measurement, there will be a 1-min break [42].

Knee extensors and knee flexors will be assessed while in sitting position at 90° hip and knee flexion [43]. The dynamometer will be placed on the anterior and posterior surface of the distal tibia 5 cm proximal to the lateral malleolus. The maximum torque reached over three repetitions of 3 s each will then be recorded and normalized to body mass (Nm/kg).

Hip abductors will be measured while in supine position and the hip in neutral abduction. The dynamometer will be placed on the lateral side of the thigh 5 cm proximal to the lateral femoral condyle. The maximum torque reaching over three repetitions of 3 s each will then be recorded and normalized to body mass (Nm/kg) [42, 43].

##### Adherence

Participants’ adherence to the home exercise program will be assessed using three methods. First, an 11-point Numeric Rating Scale (NRS) (from “completely disagree” to “completely agree”) will be used. The participants will rate up to what extent they agree with the following two statements: “I have been doing my exercise sessions every day as recommended” and “For each exercise, I have been doing the number of repetitions recommended.” Second, according to WeChat and outpatient records, the number of prescribed exercise sessions completed within the last week will be measured at specific time points, with scores ranging from 0 to 7. Third, the Exercise Adherence Rating Scale (EARS) Section B will be used [44]. This questionnaire contains 16 questions, and the results will be self-reported by participants using 5-point Likert scales. The terminal descriptors range from “completely agree” (score 0) to “completely disagree” (score 4). The total score ranges from 0 to 64, with higher scores indicating a better adherence. The physiotherapist will contact participants through WeChat and supervise their exercise programs on a daily basis. If an issue hindering adherence occurs, the participant is required to report the issue to the physiotherapist. The physiotherapist will record any details of the issue in the case report form. The physiotherapist will also arrange for an additional follow-up visit as soon as possible to address the issue. All relevant data will be saved for the final analysis.

#### Additional measures

##### Adverse events

Adverse event is defined as any problem caused by the exercise program. Participants can keep in contact with the physiotherapist via WeChat and can report symptoms of discomfort when doing exercises. The physiotherapist will record any details of the adverse event in the case report form during follow-up visits, and all relevant data will be saved. A study oversight committee will monitor and handle any adverse events if deemed necessary by the chief investigator. Any participant who experiences harm from the trial will receive free treatment. In the final analysis, two specialists will confirm these adverse events.

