**Methods/design:**

In total, 114 patients with painful knee OA will be recruited from the orthopedic outpatient department of Shanghai Jiao Tong University Affiliated Sixth People’s Hospital. To compare the therapeutic effect of two different home-based exercise programs, the participants will be randomly assigned into the experimental group (leg swing exercise) or the control group (quadriceps strengthening exercise). Each participant in both groups will be required to attend five individual sessions with a physiotherapist who will teach the exercise program and monitor progress. Participants will be instructed to perform the exercises at home every day for 12 weeks. Clinical outcomes will be assessed at baseline and 12 and 24 weeks after starting the intervention. The primary outcomes are average overall knee pain and physical function in daily life. The secondary outcomes include other measures of knee pain, physical function, patient-perceived satisfactory improvement, health-related quality of life, physical activity and performance, muscle strength of the lower limb, and adherence.

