### Procedures

Eligible patients with knee OA who visit the orthopedic outpatient department of Shanghai Jiao Tong University Affiliated Sixth People’s Hospital will be identified. Primarily, the orthopedic doctor will assess the patient’s eligibility via physical examinations. Then the results of standing full-length radiography conducted within the last 6 months will be screened by an orthopedic doctor. If participants did not undergo radiography, the procedure will be performed in the hospital. After eligibility assessment and the collection of informed consent, the doctor will arrange for a meeting with the treating physiotherapist.

For participants with bilateral symptoms, both knees will be the subjects of rehabilitation. However, only the most symptomatic eligible knee (as identified according to K-L grade and pain intensity) will be selected for assessment. In cases in which bilateral knees are equally symptomatic, the right knee will be nominated.

Participants will visit the same physiotherapist five times (study weeks 1, 3, 6, 9, and 12) over the 12-week intervention and one time 12 weeks after the end of the intervention (study week 24). Baseline and follow-up assessments will be completed at the orthopedic outpatient department of Shanghai Sixth People’s Hospital. At other times, participants will be required to maintain contact with the physiotherapist. Considering that WeChat is the most common mobile social application in China and it can be easily used by elderly individuals, regular text message reminders will be sent by the physiotherapist via this application to help improve adherence. In addition, the physiotherapist can screen participants via video calls through WeChat if necessary.

During each visit, the physiotherapist will assess the adherence of participants and the progression of the home exercise program. Moreover, they will adjust the exercise program according to each participant’s progress and physical condition using the modified Borg Rating of Perceived Exertion (RPE) CR-10 scale [20, 21]. Each individual session will last about one hour. If participants show poor adherence, the causes will be analyzed in the final statistics. Clinical outcomes such as self-reported questionnaire results, physical performance, lower limb muscle strength, and adherence will be assessed 12 and 24 weeks after starting the intervention.

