## Discussion

This prospective, two-armed, single-center RCT aims to identify whether leg swing exercise, a type of traditional Chinese exercise, is effective in decreasing knee OA symptoms compared with quadriceps strengthening exercise. The results of this RCT will provide more evidence on the effects of traditional Chinese exercise on improving physical function and relieving joint pain among patients with knee OA. If proven to be effective, leg swing exercise, which is a new type of traditional Chinese exercise that is safe, cost-effective, and less cognitively demanding, can be included in the non-surgical treatment regimen for knee OA in the future.

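### Adverse events are defined by their cause, so untoward events attributed to something other than the exercise may never be counted

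*Protocol article*

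**What the plan says.** The Adverse events section (under Additional measures) gives the definition in full: "Adverse event is defined as any problem caused by the exercise program". The same section says that participants "can report symptoms of discomfort when doing exercises" to the physiotherapist by WeChat. It continues: "The physiotherapist will record any details of the adverse event in the case report form during follow-up visits". Adjudication comes last: "In the final analysis, two specialists will confirm these adverse events".

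Other parts of the article show who is in this chain. The Abstract describes "five individual sessions with a physiotherapist who will teach the exercise program and monitor progress". Procedures says: "Participants will visit the same physiotherapist five times (study weeks 1, 3, 6, 9, and 12", with one further visit at week 24. Under Blinding, participants are open to treatment, "assessors who collect physical function outcomes will be blinded", and statisticians are blinded. The physiotherapist is not listed as blinded.

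Table 1 schedules adverse events at the home-exercise visits, week 12 and week 24. The Statistical analysis section does not mention them. The Discussion describes leg swing as "safe, cost-effective, and less cognitively demanding".

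**The concern.** Usual practice separates two questions: did something untoward happen, and was it related to the intervention? The definition here merges them, so an event that nobody attributes to the exercise is not an adverse event and need not be entered as one.

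This matters more in an open-label trial of two very different exercises. Leg swing is done standing on one leg at the edge of a low platform with handrail support; the control exercise is done lying down. The same fall, sore back or knee flare could be attributed differently according to which exercise the participant was doing. If so, the recorded counts reflect attribution as well as occurrence. A later analysis cannot recover events that were never written down, so this cannot be left to an analysis plan.

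What is at stake is the completeness and fairness of the adverse event table by arm, and the support it could give to a statement that the newer exercise is safe.

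**Working it through.** The document states no adverse event rate, safety sample size or safety power, so there is no figure to reproduce. The check is mainly textual.

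**Step 1: entry condition.** Causation by the programme is part of the definition. No wider category of untoward events, with relatedness judged later, is given.

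**Step 2: who stands at the entry.** The participant reports first and is unblinded. The physiotherapist records. Since the physiotherapist teaches the allocated exercise, sees the same participant throughout and adjusts the programme, knowledge of the arm follows from the role. No other route into the adverse event record is described.

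**Step 3: what adjudication can do.** The specialists confirm the recorded events. They can remove an event from that list but have no described means of adding one.

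**Step 4: timing.** The exercise period is 12 weeks, yet Table 1 collects adverse events at week 24. An invitation framed around discomfort during exercise captures little in the second 12 weeks.

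**Step 5: other capture.** The Adherence section has issues that hinder adherence reported and entered in the case report form. The Medication use section has medication and cointerventions recorded. Both are partial, and neither is classed as an adverse event.

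**Step 6: illustration.** Only the arm size of 57 comes from the document (Sample size calculation). All risks and attribution probabilities are assumed.

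Expected recorded events per arm = 57 × true risk × probability of attribution. With equal true risks, the recorded risk ratio (leg swing to control) is the ratio of the attribution probabilities.

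True risk 20% in both arms: 57 × 0.20 = 11.4 events per arm.

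| Attribution, leg swing / control | Recorded events | Recorded risk ratio |
|---|---|---|
| 0.5 / 0.5 | 5.7 / 5.7 | 1.00 |
| 0.4 / 0.6 | 4.6 / 6.8 | 0.67 |
| 0.3 / 0.7 | 3.4 / 8.0 | 0.43 |
| 0.6 / 0.4 | 6.8 / 4.6 | 1.50 |

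The ratios are the same at true risks of 10%, 30% and 40%.

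A real difference can also be hidden. True risks of 20% (leg swing) and 10% (control), with attribution of 0.5 and 0.8, give 0.20 × 0.5 = 10% and 0.10 × 0.8 = 8%. A 10-point difference is recorded as 2 points.

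Equal attribution leaves the ratio alone but loses information. Take true risks of 20% and 40%, 57 per arm and a two-sided 5% normal-approximation test of two proportions, used only as a gauge. Power is 0.65 with full capture and 0.32 when half the events are attributed in each arm (10% against 20%).

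**The case against.** Several points on the other side are sound.

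- **No safety comparison is planned.** A reader might infer that a planned between-arm safety test is biased. The document does not support that: adverse events are an additional measure, the hypothesis concerns pain and function, and the Statistical analysis section does not mention them. What is affected is descriptive reporting by arm.
- **The physiotherapist is not said to judge causality.** A reader might infer that the physiotherapist formally decides what counts. The text assigns that decision to no one at recording, and the specialists' confirmation could be the causality judgement. The Blinding section also qualifies adverse events as caused by the programme, which is redundant under the definition, so the term may be used more loosely in practice. Even so, the definition as written sets the entry condition, and the specialists receive only what was recorded.
- **Some events are captured elsewhere.** A fall or pain that interrupts daily exercise should surface as an adherence issue. Pain scores and patient-rated change at weeks 12 and 24 need no attribution. It would be too strong to say that such events leave no trace, but they are not counted as adverse events.
- **The word safe appears in a conditional passage.** The Discussion sentence depends on the exercise proving effective and is not a conclusion from this trial's data. Eight patients also tried both exercises beforehand as a test of safety. The wording shows only that a safety statement is contemplated.
- **The illustration is assumed.** Reversing the attribution reverses the bias, and equal attribution removes it from the ratio.
- **Article detail.** Elicitation wording, form fields and whether the specialists are masked may be in the full protocol. Their absence is no finding. The definition, however, is stated here in full.

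**Conclusion.** The point holds as a weakness in a stated definition. Attribution is the condition for being recorded as an adverse event, the described route in passes through people who know the allocation, and later confirmation is limited to recorded events. Untoward events put down to other causes may go uncounted, and partial capture as adherence issues or medication changes does not close the gap.

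The size and direction of any distortion cannot be determined from the document. The assumed scenarios show recorded risk ratios from 0.43 to 1.50 when the true risks are equal, so the effect could flatter or penalise leg swing. A reader might infer that the rule favours leg swing; nothing in the document establishes that.

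The conclusion rests on one inference, that the physiotherapist knows the arm, which follows from delivering the allocated exercise. It also assumes that the definition is applied as written. The primary and secondary efficacy analyses are not affected. The change is worth making because it is cheap and lost events cannot be recovered.

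**What to change.** Define an adverse event as any untoward medical occurrence from randomisation to week 24, whatever its cause. Ask about it in the same way in both arms at every visit, including week 24. Record relatedness to the exercise as a separate field, judged by the two specialists already planned. Mask them to arm where the event details allow; mention of the platform or ankle weight will often reveal the arm, so full masking should not be promised. Report all-cause and related events by arm.

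The cost is a changed definition, one more field on the case report form and slightly more recording, with no extra staff. Timing is the main limitation. Recruitment began on 20 April 2021 and was expected to end on 30 April 2022, and this version is dated 6 March 2022, so a change would apply mainly from then onward. Events recorded before and after the change should be reported separately.
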